#### Secondary endpoint – safety

Any type of adverse event (major or minor) that arises through the period of the study (D0 to D60) will be tracked. Reports, such as pain due to the procedure (discomfort reported by the patient, caused by needle punctures, and/or agent indwell), will be evaluated using the “Patient Satisfaction Questionnaire”. Adverse events that will be directly analyzed at the secondary endpoint (Additional file 3) are stains (limited to the target area), hematomas (limited to the target area), edema, and phlebitis (limited to the target limb). DVT is a severe, but unusual, complication with few existing reports documenting its effects [15]. However, this complication will also be recorded if it occurs. All of these data will be collected during medical visits (D0 to D60).

The photos taken at the end of the study (D60) will be used to evaluate irreversible skin changes such as hyperpigmentation. Two external physicians (both vascular surgeons), blinded to which modality of treatment was carried out, will score the changes as follows: 5 (excellent – no visible hyperpigmentation at the target area); 4 (very good – presence of only one point of hyperpigmentation up to 1 cm in length at the target area); 3 (good – presence of 2 to 3 points of hyperpigmentation up to 1 cm in length at the target area); 2 (fair – presence of 4 to 5 points of hyperpigmentation up to 1 cm in length, or one hyperchromatic line, up to 5 cm in length, at the target area); 1 (bad – presence of more than 5 points of hyperpigmentation up to 1 cm in length, or one hyperchromatic line, with more than 5 cm and less than 9 cm in length, at the target area); and 0 (unsuccessful – presence of a hyperchromatic line larger than 9 cm in length, or the total extension of the vein presenting hyperpigmentation, at the target area) (Additional file 6). Any conflicting results in the scores assigned by the two judges will be handled as described in the “Primary endpoint” section above.

Other data will be gathered in the analysis such as demographic data, skin color, and skin changes at the target area (pain, phlebitis, stains). Major adverse events, such as deep venous thrombosis, will also be reported throughout the study.

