### Statistical analyses

Based on alpha = 0.05, and assuming a standard deviation in the primary endpoint score of 1.5, with 48 participants in each arm, we have >80% power to detect a minimal difference in scores of 0.9. Only one extremity will be included per patient. It is expected that 10% of patients will be lost during follow-up. To promote the most statistically rigorous method, we will use a larger sample size of at least 106 patients. Data will be evaluated either by Student’s *t*-test or non-parametric Mann–Whitney test (if relevant conditions are not met). Categorical variables (e.g., proportions) will be compared between groups using the χ^2^ or Fisher’s exact test when necessary. Scores between the groups will be compared with Mann–Whitney test. All statistical analyses will be performed using STATA® v11 (Stata Corp, College Station, TX, USA). All analyses will be performed on an intent-to-treat basis.

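### The D60 hyperpigmentation score is compared by an unstratified Mann–Whitney test although skin colour is collected; stratifying on it may gain precision at almost no cost

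*Protocol article*

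**What the plan says.** Under Secondary endpoint – safety, the D60 photographs "will be used to evaluate irreversible skin changes such as hyperpigmentation". Two blinded external vascular surgeons give each patient a score from 0 to 5 according to the number of pigmented points or the length of a pigmented line. The same section adds: "Other data will be gathered in the analysis such as demographic data, skin color". It does not say when skin colour is recorded, in which categories, or how it enters an analysis.

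Under Statistical analyses, one sentence covers every score: "Scores between the groups will be compared with Mann–Whitney test". It names no stratification factor or covariate. Patient enrollment and randomization describes a computer-generated allocation schedule and mentions no stratification. The Hypothesis section states that the polidocanol mixture is not inferior in safety and gives no margin.

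**The concern.** The outcome is pigmentation as it appears on a photograph, so the patient's own skin colour could plausibly affect the score. If it does, the plain rank test leaves that variation in the noise, and a real difference between arms in staining becomes easier to miss. With about 48 patients per arm and no balancing, the arms may also differ in skin colour by chance, and the plain test has no means of allowing for that.

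This matters somewhat more than for an ordinary secondary outcome. The safety hypothesis is one of being no worse, and the Background and Discussion both single out blemishes or stains as an open question. The only comparison specified for the score is a test of difference, so low power could let a non-significant result pass for reassurance.

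**Working it through.** **Inputs from the protocol article (Statistical analyses)**
- Significance level and SD: "Based on alpha = 0.05, and assuming a standard deviation in the primary endpoint score of 1.5". Two-sided testing is assumed, as sidedness is not stated.
- Sample size and effect: "with 48 participants in each arm, we have >80% power to detect a minimal difference in scores of 0.9".
- Losses: "It is expected that 10% of patients will be lost during follow-up", and therefore "we will use a larger sample size of at least 106 patients". After 10% loss, 106 × 0.9 ≈ 95 patients remain, so about 48 per arm is the right basis.

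**The plan's own figure**
- SE of the difference = 1.5 × √(2/48) = 0.306.
- Power = Φ(0.9/0.306 − 1.96) = Φ(0.98) = 83.6%; the noncentral t gives 82.9%.
- With Mann–Whitney efficiency of 0.955 it is 81.9%.

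The stated power above 80% reproduces. It concerns the primary efficacy score only; no SD or power is given for the hyperpigmentation score.

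**Inputs the article does not give (assumed, shown as ranges)**
- Share of patients with darker skin (two levels): 20% to 50%.
- Variance in the score explained by skin colour (R²): 0 to 0.20.

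**Step 1: precision on a linear scale.** Adjusted SE / unadjusted SE = √(1 − R²). Equivalent unadjusted sample size = 96/(1 − R²).

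| R² | SE ratio | Equivalent N |
|---|---|---|
| 0 | 1.000 | 96 |
| 0.05 | 0.975 | 101 |
| 0.10 | 0.949 | 107 |
| 0.20 | 0.894 | 120 |

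**Step 2: chance imbalance.** SD of the between-arm difference in the share = √(2p(1 − p)/48). The last column is the exact binomial probability.

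| Darker-skin share p | SD (percentage points) | P(difference ≥ 10 points) |
|---|---|---|
| 20% | 8.2 | 25% |
| 30% | 9.4 | 32% |
| 50% | 10.2 | 36% |

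**Step 3: simulation of the two tests.** There were 48 patients per arm and 4,000 runs per scenario. A normal latent variable with residual SD 1 was cut into six ordered scores, with base proportions of 5, 8, 12, 15, 20 and 40% from score 0 to 5. The treatment shift was 0.6, the darker-skin share p was 30% or 50%, and darker skin lowered the latent value by b = 0, 0.5 or 1. R² = b²p(1 − p)/(1 + b²p(1 − p)). For b = 1 and p = 0.3 this is 0.21/1.21 = 0.174.

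| p | b | R² | Plain Mann–Whitney power | van Elteren power |
|---|---|---|---|---|
| 30% | 0 | 0 | 72.2% | 71.6% |
| 50% | 0 | 0 | 72.1% | 71.6% |
| 30% | 0.5 | 0.050 | 70.8% | 72.0% |
| 50% | 0.5 | 0.059 | 71.1% | 72.4% |
| 30% | 1.0 | 0.174 | 62.8% | 70.6% |
| 50% | 1.0 | 0.200 | 61.7% | 69.8% |

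Each power figure has a Monte Carlo SE of about √(0.7 × 0.3/4000) = 0.7 points, so the gap of about 1 point at R² near 0.05 means little or no gain.

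**Step 4: type I error (treatment shift 0).** Over all trials the plain test rejects in 4.4–5.1% and the stratified test in 4.6–5.0%. Among the 9–13% of trials with an imbalance of 15 points or more, the plain test rejects in 5–6% when R² is about 0.05 and in about 12% when R² is 0.17–0.20. The stratified test stays at about 3.5–5.3%.

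**The case against.** The strongest reply is that nothing here is wrong. An unadjusted rank test of a randomised comparison is valid, chance imbalance is already part of its 5% error rate, and the outcome is secondary and outside the power calculation. The article does say that skin colour is gathered for the analysis, so it is silent on the use rather than ruling one out. An adjusted supportive analysis could sit in a statistical analysis plan that is not shown. All of this stands, and it keeps the severity low.

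The benefit also depends on a link that the article never quantifies. Even its direction is open: stains might be harder to see on darker skin, which would raise the score, whereas the simulation lowers it. This limits what can be claimed but does not remove the point. With equal shares, reversing the direction merely swaps the labels of the two strata and leaves the result unchanged. When skin colour is irrelevant, the stratified test loses about half a point of power.

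Three stronger readings are tempting, and the article supports none of them:
- A reader might infer that the planned comparison is biased. It is not: the 12% rejection rate applies only to a badly imbalanced subset of trials under a strong assumed link, and the overall rate is about 5%.
- A reader might infer that precision is certainly lost. With no link, none is.
- A reader might infer a calculable harm to the non-inferiority conclusion. No margin is stated, and the figures above are for a test of difference.

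**Conclusion.** The point holds as a low-severity improvement, not as an error or contradiction. The article commits all scores to one unstratified test while collecting a variable plausibly related to this particular score. The gain from stratifying is nil with no link, about 1 power point at R² near 0.05, and about 8 points at R² of 0.17–0.20. In the last case it also protects against an unlucky allocation.

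These sizes rest on 48 per arm, a two-level skin-colour factor with a 30% or 50% share, and the assumed score distribution and treatment shift. The article does not say where in this range the trial lies. The case for the change is that the trade is lopsided: almost nothing is lost if skin colour is irrelevant, and a worthwhile amount is gained if it is not.

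**What to change.** 1. State that skin colour is recorded at D0, before treatment, in a few prespecified categories, with a rule for merging sparse ones.
2. Compare the D60 hyperpigmentation score between arms with a van Elteren test (stratified Mann–Whitney) using those categories. Alternatively, use a proportional-odds model with arm and skin colour, reporting the odds ratio and its confidence interval.
3. Keep the unstratified Mann–Whitney test as a sensitivity analysis.

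No extra patients, visits or measurements are needed. The cost is a short change of wording, agreement on the categories before the scores are analysed, and a check that the chosen method is available in the named STATA version. Very small strata add little information, so the categories should be few. Fixing this in advance also removes any later choice between adjusted and unadjusted results if the arms turn out to be imbalanced. The missing margin for the safety hypothesis is a separate matter, which this change does not resolve.

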### Statistical analyses

Based on alpha = 0.05, and assuming a standard deviation in the primary endpoint score of 1.5, with 48 participants in each arm, we have >80% power to detect a minimal difference in scores of 0.9. Only one extremity will be included per patient. It is expected that 10% of patients will be lost during follow-up. To promote the most statistically rigorous method, we will use a larger sample size of at least 106 patients. Data will be evaluated either by Student’s *t*-test or non-parametric Mann–Whitney test (if relevant conditions are not met). Categorical variables (e.g., proportions) will be compared between groups using the χ^2^ or Fisher’s exact test when necessary. Scores between the groups will be compared with Mann–Whitney test. All statistical analyses will be performed using STATA® v11 (Stata Corp, College Station, TX, USA). All analyses will be performed on an intent-to-treat basis.

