### Treatment area

To define the treatment area, on the outer side of the lower limbs (thigh and leg) and using the fibular head projection as an anatomical reference point, a longitudinal imaginary line measuring 25 cm (up) and 15 cm (down) will be drawn using the fibular head as a starting point. Two additional lines will be drawn parallel to the first one, with one marked at 7.5 cm anterior and the other at 7.5 cm posterior, which define the limited area for treatment (600 cm^2^; Additional file 2). In this area, one or two reticular veins, measuring from 10 cm to 20 cm in total length, will be treated with a minimum of 10, and a maximum of 30, punctures and with 5 mL as the maximum volume of medication over the treatment duration. Each puncture will not exceed 0.3 mL of volume.

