### Photographic registry

Photos of patients will be taken to register the early and late results of the treatment area (pre-treatment). A high definition camera (D7000 Nikon™ Lens: AF-S Nikkor™ 18–105 mm 1:3.5-5.6G) will be used to obtain these pictures. The target area, described above, will be photographed before treatment (pretreatment) to prevent a possible time bias related to the patient’s illness. Patients will be placed in a standing position on a platform with the target area facing the camera, which will be placed 1.0 m away. A high-definition standardized scale (attached to the platform) will be used to perform all measurements. The room will be arranged with ideal lighting.

Pictures will be stored in files for later analysis using ImageJ™ software. Each photo will be identified with code numbers (according to the randomized number of the protocol), matching the moment of the study (Day 0 (D0) and D60). ImageJ software will be used to measure the length of the treated veins by turning pixels into centimeters using a 2 cm line drawn upon the standardized scale. Measurements will be taken from the photos before and after the study.

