### Outcomes

#### Primary endpoint – efficacy

Analysis of the primary endpoint (efficacy) will be based on the ability of each treatment to promote the disappearance of the reticular veins after 60 days of treatment (D60). Efficacy will be scored according to commonly used visual aesthetic aspects [2]. Photo analysis will be used to evaluate efficacy (from D0 to D60), which will be performed by two external physicians (both vascular surgeons) who are blinded to treatment modality. According to the image, these judges will assign scores for each patient as follows: 5 (excellent – complete healing at the target area); 4 (very good – presence of up to 1 cm of non-healed veins in length at the target area); 3 (good – presence of 1 cm to 3 cm of non-healed veins in length at the target area); 2 (fair – presence of 3 cm to 5 cm of non-healed veins in length at the target area), 1 (bad – presence of 5 cm to 9 cm of non-healed veins in length at the target area), and 0 (unsuccessful – presence of more than 9 cm of non-healed veins in length at the target area) (Additional file 5). Prior to these analyses, both judges will be trained with 10 random patients to standardize the methods of measurement.

If there are conflicting results in the scores assigned by the two judges (divergence in scores up to 1 point), a third previously trained judge will be assigned to independently score that image, and the final score will be the average of the scores from the three judges. However, if there are conflicting results in the scores assigned by the two judges (divergence in scores greater than 2 points), a conference among the two judges with a third previously trained judge will be arranged to define a consensus on the final score. All these procedures will be carried out in a blind manner.

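### The primary score counts absolute centimetres of residual vein, but treated length may vary twofold and the planned Mann–Whitney comparison does not use the baseline length already measured

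*Protocol article*

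**What the plan says.** - **Score.** Primary endpoint – efficacy defines six categories by the length of vein not healed at D60: none (5), up to 1 cm (4), 1–3 cm (3), 3–5 cm (2), 5–9 cm (1) and more than 9 cm (0). Score 1, for example, is "presence of 5 cm to 9 cm of non-healed veins in length at the target area". Starting length plays no part.
- **Starting length.** Treatment area allows one or two veins "measuring from 10 cm to 20 cm in total length".
- **Measurement.** Photographic registry has the length of the treated veins measured in ImageJ: "Measurements will be taken from the photos before and after the study". D0 length is therefore available.
- **Analysis.** Statistical analyses says "Scores between the groups will be compared with" a Mann–Whitney test. No covariate, stratum or percentage-change analysis is named there, and the randomisation text mentions no stratification by length.
- **Planning.** "Based on alpha = 0.05", "assuming a standard deviation in the primary endpoint score of 1.5", "with 48 participants in each arm", the protocol says "we have >80% power to detect a minimal difference in scores of 0.9".

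**The concern.** The endpoint is meant to capture how well each agent makes the veins disappear. A score built on absolute residual length also reflects how much vein there was at the start. Two patients with the same proportional response can fall in different categories, and the longer vein never scores better.

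Starting length thus adds variation to the score that has nothing to do with treatment. The planned comparison leaves it in the error term, although the variable that explains it is already measured. If the arms happen to differ in mean treated length, the unadjusted comparison moves with that difference. A reader of the result also cannot tell how much of a given score reflects the agent and how much the starting length.

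**Working it through.** **1. The plan's own figure.** Inputs from Statistical analyses: 48 per arm, difference 0.9, SD 1.5, alpha 0.05 (two-sided assumed, since the protocol does not say). Standardised difference = 0.9/1.5 = 0.6. Two-sample t-test power is 82.9% (83.6% by the normal approximation), so the stated figure of more than 80% reproduces.

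**2. What a score means at each end of the length range.** Clearance = 1 − residual/starting length.

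| Score | Residual (cm) | Clearance, 10 cm vein | Clearance, 20 cm vein |
|---|---|---|---|
| 1 | 5–9 | 10–50% | 55–75% |
| 0 | more than 9 | under 10% | under 55% |

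Read the other way, for the same proportion remaining:

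| Remaining | 10 cm vein | Score | 20 cm vein | Score |
|---|---|---|---|---|
| 10% | 1 cm | 4 | 2 cm | 3 |
| 30% | 3 cm | 3 | 6 cm | 1 |
| 46% | 4.6 cm | 2 | 9.2 cm | 0 |
| 50% | 5 cm | 2 | 10 cm | 0 |

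The categories share their limits (1, 3 and 5 cm each belong to two). The table puts a limit value in the better category. The 46% row does not depend on that choice. The largest gap is two points.

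**3. How strongly length predicts the score.** The protocol gives no correlation r, so it has to be assumed. Simulation: length uniform on 10–20 cm, residual fraction from beta distributions with 0–30% of patients completely cleared, residual length cut at the protocol's limits. In 53 such scenarios with a score SD of 1.4–1.6, close to the planned 1.5, |r| ran from 0.03 to 0.24 (median 0.15). Values near 0.3 appeared only when the score SD was about 1. Values up to 0.47 needed half the veins at exactly 10 cm and half at exactly 20 cm. A working range of about 0.1 to 0.25 is reasonable.

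**4. Effect of adjustment on power.** Residual SD = 1.5 × √(1 − r²), so the standardised difference is 0.6/√(1 − r²), with 48 per arm.

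| Assumed \|r\| | Residual SD | Standardised difference | t-scale power |
|---|---|---|---|
| 0 (unadjusted) | 1.500 | 0.600 | 82.9% |
| 0.10 | 1.492 | 0.603 | 83.2% |
| 0.15 | 1.483 | 0.607 | 83.7% |
| 0.25 | 1.452 | 0.620 | 85.2% |

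Direct simulation (4,000 runs, 48 per arm, uniform lengths) of Mann–Whitney against rank ANCOVA on length:
- 72.9% to 73.5% (score SDs 1.52 and 1.35)
- 92.1% to 92.3% (SDs 1.33 and 1.24)
- 49.6% to 53.2% (SDs 1.04 and 0.97)

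The gain is thus about 0 to 3 points, and under 1 point where the SD is nearest to plan.

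**5. Chance imbalance.** SD of a uniform length = 10/√12 = 2.89 cm. Standard error of the between-arm difference in mean length = 2.89 × √(2/48) = 0.59 cm. Expected change in score per cm = r × 1.5/2.89. An imbalance of one standard error shifts the score difference by r × 1.5 × √(2/48) = r × 0.306. That is 0.03 points at |r| = 0.10, 0.05 at 0.15 and 0.08 at 0.25. An imbalance of 1.96 standard errors gives 0.06, 0.09 and 0.15 points, against the planned 0.9.

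**6. Validity of the planned test.** With no treatment effect, the simulated type I error of the plain Mann–Whitney test was 4.5–5.4%.

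**The case against.** The strongest reply is that nothing here is an error. Residual visible vein is a legitimate aesthetic endpoint, since 9 cm left looks poor whatever the starting length, and score 5 means the same at every length. Mann–Whitney is a valid test for an ordinal score, randomisation protects it, and its error rate already allows for chance imbalance in length. The gain from adjustment is small. Adjusted and supportive analyses are also often left to an analysis plan, which is not shown here.

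Much of this stands. Keeping the absolute score is defensible, the test is sound and the gain is modest. The reply does not remove the point, because the protocol itself fixes both the score and the test for it, and leaves unused a baseline value that it collects. The proposal changes a stated choice; it does not ask for missing detail.

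A reader might infer that starting length strongly determines the score, so that adjustment would lift power to 86% or 90%. Those figures need |r| of 0.30 and 0.45. Under uniform lengths, values that high do not occur together with the planned SD of 1.5.

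A reader might also infer that an odds ratio from a proportional-odds model is the natural remedy. It would not give an estimate on the 0.9-point planning scale. Averaging three judges' scores also produces fractional values, which such a model does not take without further rules.

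**Conclusion.** The concern holds as a matter of precision and interpretability. Equal proportional clearance can score up to two points apart, and the planned comparison leaves out the length that explains it. For |r| of 0.1 to 0.25, adjustment raises t-scale power from 82.9% to about 83–85%, and rank ANCOVA gains about 0 to 3 points. A chance imbalance in length at the 1.96 standard error limit would move the score difference by 0.06 to 0.15 points.

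These sizes rest on lengths uniform over 10–20 cm, a score SD near 1.5 and assumed clearance distributions. The protocol gives no data on any correlation between length and score.

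It would be wrong to conclude that the planned test is biased, that its type I error is inflated or that the sample size is mistaken. The documents and the calculations support none of these. The change is worth making because it costs almost nothing, and its main benefit is a clearer reading of the result.

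**What to change.** Before any D60 data are analysed (Preliminary results states that no patient had yet reached D60), pre-specify the following:

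1. A primary comparison of D60 scores adjusted for D0 ImageJ treated length, by rank ANCOVA or by a van Elteren test stratified by length. Both accept the fractional scores that arise when judges are averaged. Choose one and, for van Elteren, fix the length strata in advance.
2. The mean score difference adjusted for D0 length, with its 95% CI, for example from a linear model of score on arm and length. This puts the estimate on the same scale as the planned 0.9 points.
3. The unadjusted Mann–Whitney test, kept as a sensitivity analysis.
4. Percentage of treated length cleared, from the ImageJ measurements at D0 and D60, as a supportive analysis.

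The cost is revised analysis wording and slightly more analysis work. No patient, visit or new measurement is needed.

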**Methods/design:**

Inclusion criteria are women between 18 and 69 years old with at least 10 cm long reticular veins in the lower limbs, on the outer side of the leg/thigh. Patients with CEAP 2 to 6, or with allergies, pregnancy, performing breastfeeding, or with any dermatologic or clinical problems will be excluded. Patients with venous ultrasound mapping showing involvement of saphenous trunks and/or a deep venous system will also be excluded. Patients will be randomized into two groups, one receiving 75% pure glucose and the other group receiving 0.2% polidocanol diluted in 70% glucose. Just one limb and one session per patient will be performed. The sclerosing agent volume will not exceed 5 mL. Clinical follow-up will include visits on days 7 and 60, always with photographic documentation.

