### Hypothesis

We hypothesize that 0.2% polidocanol plus 70% hypertonic glucose is superior to 75% hypertonic glucose alone in promoting the disappearance of reticular veins of the lower limbs. Moreover, we hypothesize that 0.2% polidocanol plus 70% hypertonic glucose is not inferior to 75% hypertonic glucose in terms of safety.

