### Preliminary results

Forty-eight patients are currently enrolled; 25 patients have received treatment, 2 patients were excluded due to selection error, and 22 showed no major adverse effects during D7. However, the majority of patients had small local hematoma. Nevertheless, determining the efficacy of the sclerosing agent is currently not possible, given that no patient reached D60. We expect to answer some questions regarding the safety and efficacy of these sclerosing agents, including the advantages and limitations of each. Finally, we hope to determine the superiority of one agent over the other.

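### Intent-to-treat is fixed for every analysis, safety included; if any randomised patient is never injected and is counted as event-free, the harm comparison is distorted, though probably only slightly

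*Protocol article*

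**What the plan says.** The Statistical analyses section closes with a blanket rule: "All analyses will be performed on an intent-to-treat basis". The article defines no safety set or as-treated set anywhere.

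Three other places bear on how that rule works for safety:

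- The Hypothesis section states that polidocanol plus glucose "is not inferior to 75% hypertonic glucose in terms of safety". It gives no margin.
- The safety endpoint section says "Any type of adverse event (major or minor) that arises through the period of the study (D0 to D60) will be tracked". It names stains, hematomas, edema and phlebitis for direct analysis, alongside procedural pain and a hyperpigmentation score read from the day-60 photographs.
- The abstract limits exposure: "Just one limb and one session per patient will be performed".

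For event proportions the planned comparison is a test of difference: "Categorical variables (e.g., proportions) will be compared between groups using the" chi-square or Fisher's exact test.

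**The concern.** Intent-to-treat is the natural basis for the superiority question on efficacy, where dilution works against the claim. The safety question runs the other way. The trial hopes to show that polidocanol is no worse, and anything that shrinks a real difference helps that conclusion.

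The safety events follow from the injection. A woman who is randomised but withdraws before day 0, or is found unsuitable that day, cannot have a sclerosant reaction. If she stays in her arm's denominator with no event, she lowers that arm's apparent rate. The same rule would also charge a reaction to the allocated agent if a different solution had been given.

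This is not a detail left to a fuller document. The article states the analysis basis and applies it to everything.

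**Working it through.** **The plan's own figures.** The only power statement concerns the efficacy score: SD 1.5, difference 0.9, 48 per arm, two-sided alpha 0.05 (sidedness assumed).

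- Standard error: 1.5 × √(2/48) = 0.306.
- Power: Φ(0.9/0.306 − 1.96) = 83.6% (82.9% by noncentral t). This agrees with the stated figure of more than 80%.
- Sample size: 96 × 1.10 = 105.6, the stated 106; 96/0.90 = 106.7 would give 107. The gap is immaterial here.

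None of this sizes the safety comparison. It supplies only the arm size used below, 106/2 = 53.

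**Formula.** Let p_P and p_G be the event rates among injected patients, and u_P and u_G the shares randomised but never injected. If uninjected patients are scored as event-free,

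intent-to-treat difference = p_P(1 − u_P) − p_G(1 − u_G).

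With u_P = u_G = u this is (1 − u)(p_P − p_G).

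**Scenarios.** The article gives neither event rates nor u, so all of these are assumptions. Take p_P = 40%, p_G = 30% (true excess 10 points) and 5 of 53 untreated (9.4%) where shown. Then 0.40 × 48/53 = 36.2% and 0.30 × 48/53 = 27.2%.

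| Never injected | Polidocanol | Glucose | Apparent excess (points) |
|---|---|---|---|
| None | 40.0% | 30.0% | 10.0 |
| 5 in each arm | 36.2% | 27.2% | 9.1 |
| 5 in polidocanol only | 36.2% | 30.0% | 6.2 |
| 5 in glucose only | 40.0% | 27.2% | 12.8 |

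The excess of 9.1 is 4.8/53, taken before rounding the two rates.

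**Against sampling error.** The standard error of the difference at 40% and 30% is √[(0.40 × 0.60 + 0.30 × 0.70)/53] = 9.2 points. The balanced shift of 0.9 points is about one tenth of that.

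**Range over u (balanced).** With other assumed rates, 25% and 10%, the difference among injected patients is 15.0 points. Under intent-to-treat it becomes 14.4 at u = 4%, 14.25 at 5%, 13.5 at 10% and 12.0 at 20%.

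Suppose, for illustration, that a margin existed and equalled the true 15 points. A nominal one-sided 2.5% rate of falsely declaring non-inferiority would then be about 3.0% at u = 4%, 4.1% at 10% and 6.6% at 20%.

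**The case against.** The strongest reply has five parts.

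1. **The mechanism is conditional.** Safety data are collected at visits, pain on a form about the treatment, and hyperpigmentation from day-60 photographs. A woman never injected may simply have no data, and nothing says that missing means no event. This stands. The dilution formula applies only where such women are counted as event-free.

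2. **The direction is not fixed.** A reader might infer that the rule always pulls toward the hoped-for safety result. The glucose-only row, at 12.8 points, shows that it need not. Only a balanced share combined with a true polidocanol excess gives that pull reliably. This stands.

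3. **A one-arm imbalance is unlikely.** The trial is described as triple-blind, and syringes are prepared in a separate room and labelled only by number. Withdrawal before injection should not depend on arm. If five such patients fell at random, all five would be in the polidocanol arm with probability 0.5^5, about 3%. This stands.

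4. **The share is unknown.** The Preliminary results section reports "Forty-eight patients are currently enrolled; 25 patients have received treatment", and a reader might take the other 23 as randomised and never injected. The text does not support that: recruitment was still under way and their randomisation status is not given. Nor does it say whether the 2 excluded for selection error had been randomised. The 10% loss allowance concerns follow-up, so on its wording it describes women already treated. No wrong-syringe event is reported either.

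5. **A larger weakness sits beside this one.** With no margin and only difference tests, the non-inferiority hypothesis cannot be tested as written. That is true and separate. It does not make intent-to-treat a suitable basis for the harm comparison.

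What survives is that the rule is explicit, covers safety and suits that endpoint poorly. Withdrawal is allowed at any time, and duplex ultrasonography falls between clinical inclusion and treatment, so a randomised but uninjected patient is possible, though not shown.

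**Conclusion.** The point holds in conditional form and is minor. The article fixes an analysis basis for safety that can distort a no-worse comparison if any randomised patient is never injected and is scored as event-free. A balanced share u removes the fraction u of the difference; an unequal share can move it either way. The expected size is small. On the assumed rates, about 9% untreated in each arm costs 0.9 points out of 10, well inside sampling error, and with everyone injected there is no effect.

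The document does not support the stronger claims that uninjected patients are known to exist among those randomised, or that the safety result is biased in polidocanol's favour. The event rates and untreated shares used here are assumptions.

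**What to change.** Limit the intent-to-treat sentence in the Statistical analyses section to the efficacy endpoint. State that the safety outcomes will be analysed in all patients who received at least one injection, grouped by the solution actually received. Report the number randomised but not injected in each arm, with the reason.

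The cost is a sentence or two; visits, sample size and data collection are unchanged. The downside is that the safety set is no longer strictly the randomised set, so it would lose some protection if failure to be injected differed between arms. The reported counts would let a reader see that. If every randomised patient is injected with the allocated solution, the two sets are identical and nothing is lost.
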